### Randomization of groups

After subjects provide signed written informed consent, they will be classified randomly. From a common database, subjects will be computer-assigned to the intervention group and non-intervention (control) group in each PCC, proportionally to the total number of subjects. Subjects who choose not to participate in the study will be replaced by others of the same sex, age, and PCC to obtain the initial total sample of 97 subjects in each group.

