### Intervention

Educational session aimed at caregivers: A one-hour, standardized educational session, conducted by a nurse in small groups of 15 caregivers will have the following content:

• Nutritional value of food.

• Designing a healthy diet.

• Advice on dietary adaptation to address the most common nutritional problems in this group, such as energy, protein, vitamin, mineral and water deficiency, and adaptation of textures.

• Recommendations on basic cooking techniques.

Monitoring of educational intervention: PCC nurses will monitor patients monthly at home up to 6 months and then at 12 months.

To provide individualized dietary advice as necessary, standardized ad hoc cards have been developed with all the predictable interventions.

Controls: Control subjects will not receive nutritional intervention; they will be visited once to complete an initial assessment and will receive regular Home Care follow-up at 6 months and 12 months.

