### Statistical analysis

#### Sample size

The main variable is the MNA score. This value has an approximate average of 25.4 and standard deviation of 3.7 points in the Spanish population [15]. It is considered that variation of 2 points is a clinically relevant value. Considering a one-sided hypothesis and admitting an alpha error of 0.05 and a power of 95%, a sample of 72 subjects in each group is needed to observe a difference of 2 points in the MNA test after educational intervention with a precision of 80%. Taking into account possible losses during follow-up, the sample expands by 20% (15 subjects) so that the study includes 87 subjects in each group, a total of approximately 200 patients.

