#### Analysis strategy

Variables will be described as mean and standard deviation and percentages for quantitative and qualitative variables respectively. Comparison of quantitative variables will use Student-Fisher *T* test and analysis of variance for categorical variables and the chi-square statistical test. Standard tests (Kolmogorov-Smirnov and Shapiro-Wilks) will be used to verify the hypothesis of normal distribution of quantitative variables. If the preconditions for the application of statistical tests are fulfilled non-parametric tests will be used.

Longitudinal studies with a control group, which act in a phased manner on the caregiver-patient to see the effect on the patient, have different directions of analysis: caregiver assessment to measure acquisition of knowledge and implementation of dietary advice, and patient assessment to measure the effectiveness of educational intervention on nutritional status (MNA, diet, anthropometry, biochemistry) at 6 and 12 months in the intervention and control group and between groups.

To evaluate these effects, multivariate models of multiple linear regression and logistic regression will be created.

To measure the effect of educational intervention on the patient’s nutritional status (MNA, diet, anthropometry, biochemistry), the results will be adjusted according to degree of knowledge acquisition and implementation of dietary advice, as well as other variables that may interfere with the patient’s nutritional status such as socio-economic characteristics, caregiver education levels, and patients’ chronic diseases, dental status, degree of dependence (Barthel test), cognitive function (Pfeiffer Test), or mood (Yesavage Scale).

Initially the inclusion in the model of all variables that are part of the theoretical model will be forced, and in a second phase there will be an automatic selection by the stepwise method (backward and forward) to get reduced models.

The conditions of application of the models will be verified by standard techniques that are primarily based on analysis of the residuals.

The bilateral null hypothesis of normality, no difference and no significance of regression coefficients, will be discarded when their probability is less than 5%.

For data analysis the latest version of the software package SPSS/PC for Windows will be used.

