Study results will be obtained for the main variable MNA test, a validated screening test with a sensitivity of 80% and a specificity of 90% [14], and also using other outcomes measures like anthropometric measurements (estimated according to standard recommendations), a validated food frequency questionnaire, and biochemical markers. Standard laboratory methodology will be followed for extraction, transport, treatment and storage of the samples, which will be frozen for simultaneous analysis to avoid analytical variability.

Losses to follow-up are a limitation of longitudinal studies. Moreover, in dependent patients, the loss is very high due to their serious health condition. The 20% increase over the minimum required sample and the effect at 6 months will be calculated for intermediate reporting in the case of subjects lost to follow-up.

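### The effect model names neither baseline MNA nor the PCC within which patients are allocated, and does not protect them from stepwise removal; this costs precision but does not bias the comparison

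*Protocol article*

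**What the plan says.** The Analysis strategy section of the protocol article plans t tests, analysis of variance and chi-square tests, then multiple linear and logistic regression. The effect on nutritional status is adjusted for caregiver knowledge, uptake of dietary advice and an illustrative list of other variables: socio-economic characteristics, caregiver education, chronic diseases and "dental status, degree of dependence (Barthel test), cognitive function (Pfeiffer Test), or mood (Yesavage Scale". All variables of a theoretical model, not itemised further, are forced in first. Backward and forward stepwise selection then produces reduced models. Baseline MNA and PCC are not named.

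Both are available. The Study population and Recruitment sections make a baseline MNA of 17 to 23.5 a condition of entry, so every patient has one. The section on randomisation assigns patients "in each PCC, proportionally to the total number of subjects".

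On timing, Outcomes Assessment schedules measurement at 6 and 12 months, and Analysis strategy assesses effectiveness at both. No repeated-measures model and no primary visit are named. The Discussion adds that "the effect at 6 months will be calculated for intermediate reporting in the case of subjects lost to follow-up".

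**The concern.** The baseline value of an outcome is usually its strongest single predictor. A factor within which allocation was made normally belongs in the analysis. A plan that lists dental status and mood by name but not these two has fixed its adjustment set in some detail and missed the two most natural members.

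The stepwise phase adds to the problem. It keeps or drops terms according to the observed data, so a covariate that should stay by design has no guaranteed place in the reported model.

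What is at stake is efficiency and clarity: a wider interval than the data allow, and an estimate that carries whatever imbalance in baseline MNA arose by chance.

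**Working it through.** **Inputs from the Sample size section.** Difference 2 MNA points; SD 3.7; 72 per group; a 20% addition for losses, giving 87. The planning basis is "Considering a one-sided hypothesis and admitting an alpha error of 0.05 and a power of 95"%, while Analysis strategy tests a two-sided hypothesis at 5%.

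**Inputs assumed, because the documents give none.** Baseline to follow-up correlation r = 0.3 to 0.5. ICC by PCC 0.01 to 0.10. Losses of 10% to 15% by month 6 and 20% to 35% by month 12. Correlation between the two follow-up visits 0.5 to 0.7.

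**1. The plan's own figure.** n = 2 × [SD × (z for alpha + z for power) / difference]².
- One-sided 5%, 95% power: 2 × (3.7 × 3.290 / 2)² = 74.08, so 75, against the stated 72.
- Two-sided 5%, 90% power: 2 × (3.7 × 3.242 / 2)² = 71.92, so 72.

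The mismatch is a separate matter. What counts here is that the calculation uses the raw SD, so the sample size does not rely on any gain from adjustment.

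**2. Baseline MNA.** Adjustment multiplies the residual variance by 1 − r²: 0.91 at r = 0.3 (9% less) and 0.75 at r = 0.5 (25% less). With 87 per group and 20% lost, 87 × 0.8 = 69.6, about 70 per group. By normal approximation, two-sided 5%:

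| Analysis | SE of the difference | 2 / SE − 1.96 | Power |
|---|---|---|---|
| Unadjusted | 3.7 × √(2/70) = 0.625 | 1.24 | 89% |
| r = 0.3 | 0.625 × √0.91 = 0.597 | 1.39 | 92% |
| r = 0.5 | 0.625 × √0.75 = 0.542 | 1.73 | 96% |

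**3. Upper end of r.** Eligibility narrows baseline MNA to a range of 6.5 points. If scores were roughly uniform, their SD would be 6.5 / √12 = 1.88. With a follow-up SD of 3.7 and a slope of at most 1, r cannot exceed 1.88 / 3.7 = 0.51. So 25% is close to a ceiling under these assumptions.

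**4. Chance imbalance.** In an unadjusted comparison, a baseline difference of one standard error shifts the estimate by r × SE: 0.3 × 0.625 = 0.19 to 0.5 × 0.625 = 0.31 MNA points, against a target of 2.

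**5. PCC.** Removing between-centre variation multiplies the variance by 1 − ICC: 0.99 to 0.90, or 1% to 10% less. At the stated planning inputs, n falls from 75 to between 74 and 67. Because allocation is within PCC, leaving PCC out tends to make the reported SE too large rather than too small.

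**6. Joint use of both visits.** If patients are lost for good and completely at random, the variance of the 12-month mean relative to completers only is (1 − r²) + r² × n12/n6, where r is now the correlation between visits.
- Losses 10% and 20%: n12/n6 = 69.6/78.3 = 0.889. Relative variance 0.972 (r = 0.5) or 0.946 (r = 0.7).
- Losses 10% and 30%: 60.9/78.3 = 0.778. Relative variance 0.944 or 0.891.
- Losses 15% and 35%: 56.55/73.95 = 0.765. Relative variance 0.941 or 0.885.

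The gain is about 3% to 12% of variance.

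**The case against.** The strongest reply is that the covariate list is illustrative and the theoretical model is not itemised, so baseline MNA and PCC are unnamed rather than excluded. A condensed article may leave the full list to another document. That stands as to wording: the text does not say that these variables will be left out. It does not remove the point, because the article itself fixes a stepwise phase from which no covariate is exempt.

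A second reply concerns size. The power figures compare adjustment with an unadjusted test, whereas the plan already adjusts for dependence, cognition, mood, chronic disease and dental status. If these explain part of follow-up MNA, the added gain is smaller. That stands too. At r = 0.3 the gain is under 3 percentage points of power even against the unadjusted test.

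Stronger readings are tempting, but the documents do not support them:
- *The two visits are analysed separately.* This is a fair inference from t tests and ordinary regression, but no such rule is stated.
- *Data from patients lost after 6 months are wasted.* Those data serve the 6-month effect. At most they do not inform the 12-month estimate.
- *The headline visit depends on the observed losses.* Outcomes Assessment and Analysis strategy commit to both visits unconditionally, and the Discussion speaks only of "the effect at 6 months will be calculated for intermediate reporting in the case of subjects lost to follow-up". It states no switch.
- *The 12-month result is biased because sicker patients leave.* The Discussion expects high, health-related loss, but not loss that differs by arm. Similar loss of sicker patients in both arms need not bias the arm difference.
- *Teaching sessions make the intervals too narrow, or two visits inflate the error rate.* Sessions are "conducted by a nurse in small groups of 15 caregivers", so clustering is possible, but any size rests on an assumed ICC. With 87/15 = 5.8 to 97/15 = 6.5 sessions, or 8 if each PCC holds one, a session variance in one arm would be poorly estimated. Any figure for two-visit error likewise rests on an assumed correlation.

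**Conclusion.** The point holds as one of efficiency and clarity. Neither baseline MNA nor PCC is named, and neither is protected from stepwise removal, although the first is measured on every patient and allocation is made within the second. The omission does not bias the randomised comparison, and the sample size does not depend on it.

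The correlation and ICC are assumptions, so the sizes in the working are indicative. The baseline gain probably lies towards the lower end, given the restricted entry range and the covariates already listed. The PCC gain and the gain from joint modelling of the visits are modest. That baseline adjustment helps at any non-zero correlation does not depend on the assumed values.

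**What to change.** State in Analysis strategy that the between-arm MNA comparison always includes baseline MNA and PCC as covariates, and that both are exempt from stepwise selection.

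Preferably, fit 6 and 12 months together in one repeated-measures mixed model with arm, visit, arm-by-visit interaction, baseline MNA and PCC. Patients lost after 6 months then also inform the 12-month estimate. Name one visit as primary. Session clustering can be left to a sensitivity analysis.

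The cost is one degree of freedom for baseline MNA, seven for eight PCCs, and a little more analysis work. No new measurement is needed for the main change; a session sensitivity analysis would need session membership to be recorded.

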### Caregiver variables in the intervention and non-intervention groups

These variables will be collected at baseline for both groups, except for the assessment of knowledge acquisition, which will be collected in the intervention group before the intervention, immediately after, and at 1–6–12 months thereafter.

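### The models meant to measure the intervention effect go through an automatic stepwise phase that does not exempt the arm term, and no model is named as the one that carries the conclusion

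*Protocol article*

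**What the plan says.** All of this stands in the Protocol article under Analysis strategy. The section plans simple between-group comparisons (t test, analysis of variance, chi-square). It then turns to the effects on caregiver and patient: "To evaluate these effects, multivariate models of multiple linear regression and logistic regression will be created". For the patient's nutritional status, "the results will be adjusted according to degree of knowledge acquisition and implementation of dietary advice", and also for socio-economic characteristics, caregiver education, chronic diseases, dental status, dependency, cognition and mood.

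The models are built in two steps. In the first, "Initially the inclusion in the model of all variables that are part of the theoretical model will be forced". After that, "in a second phase there will be an automatic selection by the stepwise method (backward and forward) to get reduced models". One significance rule covers everything: the null hypotheses of normality, "no difference and no significance of regression coefficients, will be discarded when their probability is less than 5" percent.

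The section does not say that arm stays in during the second step, and does not say that arm is a candidate for removal. It does not say which of the resulting estimates answers the trial's question.

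**The concern.** In a randomised trial the model exists to estimate the arm effect, so its terms should be fixed before the outcome data are seen. Here forced entry belongs to the first phase only. The second phase is described as automatic, and no term is protected.

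Two things are at stake. First, if arm is kept only when its p-value is small enough, the kept estimates are the larger ones. They are biased away from zero, and the usual interval takes no account of how they were chosen. Second, even if arm is always kept, the plan yields an unadjusted estimate, a full-model estimate and one or more reduced-model estimates. It gives no rule for choosing among them.

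**Working it through.** **Inputs.** SD 3.7 ("approximate average of 25.4 and standard deviation of 3.7 points"), design effect 2 points and 72 per group before losses all come from the Sample size section. The article gives no entry or removal thresholds, so removal at p > 0.05 and at p > 0.10 is assumed.

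**The plan's own figure.** The stated basis is "Considering a one-sided hypothesis and admitting an alpha error of 0.05 and a power of 95" percent. The normal formula n = 2(z_α + z_β)²σ²/δ² gives 2 × (1.645 + 1.645)² × 3.7²/2² = 74.1, so 75 per group, not 72. Power at 72 is 94.5%. Two-sided 5% with 90% power gives 2 × (1.960 + 1.282)² × 3.7²/2² = 71.9, so 72. This mismatch is a separate matter and does not affect the present point. The figure of 72 is used below as given.

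**Step 1: analytic check, arm eligible for removal.** SE = 3.7 × √(2/72) = 0.617. Arm is kept if |estimate| > c, with c = 1.960 × 0.617 = 1.209 (5%) or 1.645 × 0.617 = 1.014 (10%). For true effect d, let P be the probability of being kept. Then

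mean if kept = d + SE × [φ((c − d)/SE) − φ((−c − d)/SE)] / P.

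Example, d = 1 at 5%: (1.209 − 1)/0.617 = 0.338 and P = 0.368. The mean is 1 + 0.617 × (0.3768 − 0.0007)/0.368 = 1.63.

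| True effect | Kept (5% / 10%) | Mean if kept (5% / 10%) | Ratio to truth (5% / 10%) | 95% interval coverage if kept (5% / 10%) |
|---|---|---|---|---|
| 0 | 5% / 10% | 0 / 0 | – | 0% / 50% |
| 0.5 | 13% / 21% | 1.45 / 1.27 | 2.90 / 2.55 | 78% / 85% |
| 1 | 37% / 49% | 1.63 / 1.50 | 1.63 / 1.50 | 93% / 95% |
| 1.5 | 68% / 79% | 1.82 / 1.73 | 1.22 / 1.15 | 96% / 97% |
| 2 | 90% / 95% | 2.12 / 2.07 | 1.06 / 1.04 | 97% / 97% |

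At 87 per group the ratios at 5% are 2.69, 1.51 and 1.03 for true effects of 0.5, 1 and 2. At 10% they are 2.38, 1.40 and 1.02.

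**Step 2: simulated backward elimination.** Assumptions: 72 per arm, 10 baseline candidates of which 3 are prognostic with R² 0.30, removal at p > 0.10, 2000 runs.

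| True effect | Kept, arm eligible | Mean if kept | Coverage if kept | Mean, arm forced in | Coverage, arm forced in |
|---|---|---|---|---|---|
| 0 | 11% | 0.02 | 45% | 0.01 | 94% |
| 0.5 | 25% | 1.14 | 86% | 0.52 | 94% |
| 1 | 60% | 1.34 | 95% | 1.01 | 95% |
| 2 | 99% | 2.05 | 96% | 2.01 | 93% |

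The ratios (2.3, 1.34, 1.02) are lower than in Step 1 because the covariates cut the residual SD to 3.7 × √0.7 = 3.10, and so the SE to about 3.10 × √(2/72) = 0.52.

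A second simulation used 12 covariates explaining 25% of variance. At a true 1 point, arm was kept in 44% of trials with mean 1.49 (5%) and in 57% with mean 1.38 (10%). At 0.5 points the means were 1.25 and 1.17.

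**Step 3: arm forced in, covariates still selected.** In Step 2 the estimates are then essentially unbiased. Type I error is 6.1%, with Monte Carlo SE √(0.05 × 0.95/2000) = 0.5 percentage points. That suggests at most slight inflation.

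**The case against.** The best defence is that arm was never meant to be a candidate. The variables named are adjusters, and stepwise selection may be intended to thin these alone. This is a condensed article, and thresholds, protected terms and the choice of primary model are commonly left to a statistical analysis plan that is not shown. This much stands: arm's eligibility is inferred from silence, and the absence of thresholds is no fault in itself. It does not remove the point, because stepwise selection within the effect models is a stated method and not an omitted detail.

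Four stronger readings are tempting and not supported.

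- A reader might infer that the trial's effect will be taken from the stepwise model. The article does not say so.
- A reader might infer that no effect is reported if arm is dropped. The t test and the forced full model each give an estimate without selection.
- A reader might take 0% coverage at the null as a striking result. At the 5% threshold it holds by construction, since arm is kept only when the interval excludes zero.
- A reader might infer that knowledge or adherence will displace arm. In an assumed case where one such term carries the whole 2-point effect, arm was kept in about 12% of runs when eligible, and its coefficient averaged about 0 when forced in. But that case needs values for controls. Knowledge is "assessment of knowledge acquisition, which will be collected in the intervention group before the intervention" and at later times, and the adherence questionnaire is likewise for that group only. What happens depends on how controls are coded, which is not stated. Adjusting for such variables is a separate problem.

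It is also fair to say that forcing arm in would by itself remove the exaggeration, and that at the effect the trial was designed for the distortion is small.

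**Conclusion.** The point holds in conditional form. Automatic stepwise selection is planned inside the models for the randomised comparison, with no exemption for arm and no model designated to carry the conclusion.

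If arm is eligible, the exaggeration given that it is kept is about 1.3 to 1.6 times at a true 1 point, more than double at 0.5, and about 2% to 6% at 2 points. Interval coverage given retention falls to 78% to 86% at 0.5 points and to 50% or less at the null. At 1 point and above it is near nominal or slightly over. These sizes rest on 72 per arm, SD 3.7, the assumed thresholds and, in the simulations, the assumed covariate structure.

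Smaller true effects cannot be ruled out: the Background section itself cites caregiver education programmes that were not shown to work. If arm is always kept, what remains is the free choice among models and a possible slight inflation of type I error. The change is worth making but does not threaten the trial's validity as such.

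**What to change.** Drop the stepwise phase from every model used to estimate a between-group effect. Take the effect from one prespecified model with arm, the baseline value of the outcome, PCC (assignment is made within PCC, under Randomization of groups) and a short named list of baseline covariates, none removable. State that this model carries the conclusion and that the unadjusted comparison is supportive. If a search for predictors of nutritional status is wanted, keep it as a separate analysis, label it exploratory and draw no intervention effect from it.

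The cost is one deleted sentence and one added list. Reduced models would no longer support the effect claim, and a few covariates with little prognostic value may stay in the model. Both are minor.

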### Ethical Approval

The study protocol was approved by the Ethics Committee of the Institute of Primary Care Research (IDIAP) Jordi Gol on April 27, 2009.

## Discussion

Conducting a randomized intervention study allows us to compare the effect of an educational intervention about nutritional aspects between two groups, intervention and control, and random geographic location of the subjects avoids bias.

Inclusion of the PCCs of our area is randomized and stratified representing different geographical areas according to various categories: rural, urban, city center and suburb. The inclusion in the study of all patients in the Home Care program of the selected PCCs is impor-tant to avoid selection bias.

Educational intervention is aimed to caregivers because its efficacy in improving the health of dependent patients has been observed. Inclusion of the educational intervention in a Home Care Program already being carried out by nurses facilitates the conduct of the study and guarantees continuity if positive results are obtained.

The same assessment methodology will be used for the intervention and non-intervention groups and different nurses will conduct the groups to avoid influence between groups in the majority of the centers, except in the smallest centers where the same nurse will necessarily conduct both groups.

Education will be standardized among the nurses and will use the North American Nursing Diagnosis Association (NANDA) methodology specific to the nursing profession. Nursing diagnosis is the clinical judgment about an individual response to life processes, including real or potential health problems, and provides the basis for the choice of nursing intervention in order to reach the goals or outcomes. These results should be formulated before identifying and performing interventions, which are those actions that are aimed at helping the patient to achieve the expected results based on knowledge and clinical judgment [30].

Inclusion of NANDA methodology will improve the effect of early education of caregivers because it continues nutritional counselling in a direct and personalized way, nurses will use their own professional methodology, and this one is internationally accepted.

Study results will be obtained for the main variable MNA test, a validated screening test with a sensitivity of 80% and a specificity of 90% [14], and also using other outcomes measures like anthropometric measurements (estimated according to standard recommendations), a validated food frequency questionnaire, and biochemical markers. Standard laboratory methodology will be followed for extraction, transport, treatment and storage of the samples, which will be frozen for simultaneous analysis to avoid analytical variability.

Losses to follow-up are a limitation of longitudinal studies. Moreover, in dependent patients, the loss is very high due to their serious health condition. The 20% increase over the minimum required sample and the effect at 6 months will be calculated for intermediate reporting in the case of subjects lost to follow-up.
